**3.3.4. Description of the drug to be studied.**

Mifepristone

1. Chemical name: 17beta-hydroxy-11beta-[p-(dimethylamino)-phenyl]-17-(1-propynyl)estra-4,9-dien-3-one
2. Chemical structure:

1. Empirical formula: C29H35N1O 2
2. Route of administration: oral tablets
3. Amount present per tablet: 200 mg (divided into 4 parts of approximately 50mg)

**3.3.5. Admission procedure**

Eligible patients admitted for hysterectomy will be admitted to the study after they have given their informed consent. Forty subjects will be recruited. The following information will be recorded:

-general and gynecological history

-details of normal cycle (duration of cycle and of menstrual bleeding

-height and weight

-a pelvic examination will be done

**3.3.6. Duration of the project**

It is estimated that 22 months will be required for recruiting the subjects and performing the examinations and 2 months for data analysis.

**3.3.8-10 Data management and analysis**

# All data will be recorded in the patients file. The analysis of data will be done at the center

## Laboratory analysis

# Hormone analyses will be preformed at the department of Clinical Chemistry.

# Breast tissue will be analysed in collaboration with [name]. KS.

Myometrial bioses will be analysed together with Associate [name] KK, UAS. Part of the biopsies from the uterine fibroids and myometrium will be snap frozen and stored in liquid nitrigen until further processed. Material will undergo receptor analysis, immunohistochemistry and in situ hybridization. Part of the biospies will be embedded in paraffin and used for immunohistochemistry. Microarrays will be used to study gene expression of relevant growth factors.

## Statistics

*Sample size calculation*Assuming a standard deviation of 10% in the percentage volume change, 18
 subjects per group will be required to detect a difference of at least 10%
 in the percentage volume change between the treated and the placebo groups
 with 90% power, using a one-sided 5% level test. Allowing for a 10%
 drop outs, 20 subjects per group, or a total of 40, will be recruited into
 the trial.

*Analysis*

 Myoma volume: Repeated measures analysis techniques will be used. For each group, the
 change at each time point will be compared with the baseline value and the
 percentage change with respect to baseline will be estimated. A repeated
 measures model with the baseline volume as a covariate will be used to
 compare the volume at different times between the two groups. Changes will
 be plotted on the absolute scale and will also be expressed as percentage
 change with respect to baseline.

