**3. Description of the project**

**3.1. Rationale and objectives of the study**

**3.1.1. Rationale**

Uterine leiomyomata are common pelvic tumors occurring in up to 20% of women over 30 years of age, and represent one of the most frequent indications for operative procedures in women of reproductive age. (Buttram et al 1981) The growth of the fibroids seems to be dependent of ovarian steroids and receptors for both estrogen and progesterone have been identified in fibroids (Wilson et al 1980, Soules et al 1982).

That progesterone may play a role in leiomyomata growth is further supported by the finding of a higher mitotic count in leiomyomata obtained during the secretory phase than in the proliferative phase of the menstrual cycle. (Kawaguchi et al 1989)

The antiprogesteron mifepristone is a synthetic steroid hormone that binds with high affinity to the progesterone receptor thereby preventing the effect of progesterone. Administration of mifepristone has various effects on reproductive function, depending on the dose and stage of the menstrual cycle. When administered in the follicular phase of the cycle, mifepristone inhibits the process of follicular maturation and blocks ovulation.

Previous studies have shown positive effects after treatment with mifepristone when administered 25-50 mg daily for 3 months. All women became amenorrhoeic during treatment and the size of the fibroids decreased with approximately 50% (Kettel et al 1994). Studies using even higher doses of mifepristone for longer periods than 3 months have not revealed any significant risk of endometrial hyperplasia (Murphy et al 1995).

Ovarian steroids also have an effect on breast tissue. Concern has been raised about hormone replace treatment (HRT) with estrogen and progesterone. Various antiprogestins have been proposed as effective for inhibiting tissue growth in the breast. It would therefore be of importance to evaluate the effect of antiprogestins on the breast tissue.

Apoptosis (programmed cell-death) and cell proliferation seem to be closely linked according to experimental evidence. Many proteins that can induce cell death are also components of the cell cycle (Meikrantz et al 1995, Huang et al 1997). The balance between cell proliferation and cell death determines tumor growth in the endometrium as well as in the breast tissue. Specific markers for proliferation (Ki-67) and apoptosis (proteins from the Bcl-2- family) have been identified.

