**3.3. Design and methodology**

**3.3.1. General outline**

This is a pilot study to evaluate the effect of mifepristone on uterine fibroids. The study will include 40 women with uterine fibroids, recruited from the waiting list for hysterectomy. After inclusion women will be randomized to treatment with mifepristone or a placebo (i.e B-vitamin tablets). An ultrasound examination will be performed at start and repeated every 4th week. The total volume of the uterus will be measured as well as each fibroid, and also a Doppler examination of the blood vessels to the fibroids. An biopsy from the fibroid will be obtained at the same time. Endomtrial biopsies will be obtained prior to study start and at surgery for safety reasons and will undergo histological analyses.

Blood will be drawn for analyses of liver function and hemoglobin values as well as estradiol, progesterone, LH, FSH, SHBG, androstendione and DHEAS once a month. A 24 hour urine collection for cortisol levels will be performed and a measurement of body composition with bioelectrical impedance analysis (BIA). This will give information about body cell mass, fat-free mass and total body water. These tests will be repeated after the treatment period.

Women that have not had a mammography during the last 12 months will be offered to have one before the start of the study. A fine-needle-aspiration, from one breast will be performed before, and after the treatment period, for cytological analyses of apoptotic and proliferative factors i.e. Bcl-2, Ki-67 and receptors for estrogen and progesteron. Fine needle aspirations will be performed at the Dept of Cytology, KS in collaboration with [name].

The women will be given Mifegyne 200 mg tablets or B-vitamins and instructed to divide the tablets into 4 parts. One quarter of the vitamin or Mifegyne tablet (50 mg mifepristone), will be taken orally every other day for 3 months. A diary card will be handed out for self registration of bleeding (days and amount), pelvic pain and any side effects.

After the treatment period the woman will undergo surgery as planned. After the uterus has been removed it will be weighed and biopsies from the myomas will be taken for analysis of apoptotic and proliferative factors i.e. Bcl-2, Ki-67 and steroid receptors. Finally the uterus will be examined by a pathologist as part of the usual routine procedure.

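### The 90% power was derived for percentage volume change, but the stated between-group test is a repeated measures model of volume with no decisive time point

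*Protocol*

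**What the plan says.** All the statistical text is in the protocol's Statistics section.

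- **Sizing.** "Assuming a standard deviation of 10% in the percentage volume change, 18" "subjects per group will be required to detect a difference of at least 10" percentage points "in the percentage volume change between the treated and the placebo groups", "with 90% power, using a one-sided 5% level test". After a 10% allowance for drop-out this becomes 20 per group, 40 in total. No time point is attached to the difference.
- **Analysis.** Within each group, every time point is compared with baseline and the percentage change is estimated. Between groups, a repeated measures model with baseline volume as covariate is used to "compare the volume at different times between the two groups". Percentage change reappears only as a way of expressing results alongside the plots. No between-group test of it is stated.
- **Measurements.** Section 3.3.1 has ultrasound at the start and every fourth week over 3 months of treatment, which implies about three follow-up scans. "The total volume of the uterus will be measured as well as each fibroid".
- **Background effect.** Section 3.1.1 reports from earlier work that "the size of the fibroids decreased with approximately 50" per cent.

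**The concern.** The quantity that was powered and the quantity that is tested differ within one section. The sizing assumes an effect and a scatter that are both percentages of baseline. If that is right, the absolute change and its variance both grow with fibroid size. An additive, constant-variance model of raw volume then gives the women with the largest fibroids most of the influence and is inefficient when sizes vary widely. Its estimate is a difference in volume units, not the percentage difference used to justify 40 women.

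The sizing also rests on one one-sided 5% comparison, whereas the analysis compares groups at several times without saying which comparison decides. That leaves the main result open to a choice made after the data are seen.

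**Working it through.** **1. Reproduce the plan's figure.** Inputs from the Statistics section: difference 10, SD 10, one-sided 5%, power 90%.

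n per group = 2 × (z₀.₉₅ + z₀.₉₀)² × (SD/difference)² = 2 × (1.645 + 1.282)² × 1 = 17.1, rounded up to 18. Drop-out: 18 / 0.90 = 20 per group, 40 in total.

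Power at 18 per group: 10 / (10 × √(2/18)) = 3.0, and Φ(3.0 − 1.645) = 91.2%, or 90.2% by the noncentral t. The figures are correct for percentage change at one time point.

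**2. Put the same assumptions through the stated test.** Follow-up volume = baseline × (1 + percentage change/100). Percentage change is normal with SD 10 and mean 0 (control) or −10 (treated), with 18 per group. Baseline volume is log-normal. Its spread is not in the documents, so the log-SD is an assumption, shown as a range, with CV = √(exp(log-SD²) − 1). The test is the treatment coefficient from a regression of raw volume on treatment and baseline volume, one-sided 5%. The three-visit column averages the follow-up volumes, assuming between-visit correlation 0.7 and the same 10-point effect at every visit. Simulated power:

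| Baseline log-SD (CV) | Raw volume, one visit | Raw volume, mean of three visits |
|---|---|---|
| 0.1 (10%) | 89% | 94% |
| 0.4 (42%) | 85–86% | 91–92% |
| 0.6 (66%) | 81% | 87–88% |
| 0.9 (112%) | 70–72% | 78–80% |
| 1.2 (179%) | 58% | 66% |

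Ranges show the variation between simulation runs. At one visit, a t test on percentage change has about 90% power and log volume with log baseline about 89–90%, whatever the spread.

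**3. Why the log scale keeps the power.** The effect is ln(0.90) = −0.105. The log-scale SD is about 0.10 in controls and 0.10/0.90 = 0.111 in treated women, pooled √((0.0100 + 0.0123)/2) = 0.106. The standardised effect is 0.105/0.106, about 1.0, as in the sizing, and baseline spread no longer enters.

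**4. A larger effect.** With a 50-point difference and SD 10, single-visit power is above 99% on either scale at every spread in the table.

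**5. Several time points.** Suppose success could be claimed at any of three scans, each tested at one-sided 5%. The type I error would be 1 − 0.95³ = 14.3% if the scans were independent. It would be 11.7%, 10.2% and 7.9% at between-visit correlations of 0.5, 0.7 and 0.9. At any single visit the raw-volume test itself holds its level: simulated type I error was 4.7–5.1%.

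**The case against.** Five counter-arguments deserve weight.

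- **The loss is conditional.** A reader might infer that the planned test certainly has less than 90% power. The documents do not support that. With homogeneous baselines the single-visit loss is about a point, and averaging three visits takes power above 90% at small spreads. A shortfall remains at wide spreads. If the effect builds up over the visits, averaging helps less.
- **The effect may be much larger.** The 10 points are a minimum detectable difference, and at the 50% reduction cited in the Rationale the power concern disappears. That stands, but the protocol chose 10 points to justify its size and 90% is claimed for that value.
- **No rule says any visit wins.** A reader might infer three chances to declare success. The text describes one repeated measures model, from which a single overall or group-by-time test is a usual result. The 8–12% belongs to a rule that is neither stated nor excluded.
- **Transformation and contrast are often left to the SAP.** The text mentions the absolute scale only for plots and excludes no transformation. Untransformed volume is nevertheless its plain reading, and the mismatch with the sizing is in what the protocol does state.
- **Fibroids and women.** Scanning every fibroid while counting women might suggest that fibroids are treated as independent units. The protocol is only silent on how they are combined; that is not a contradiction.

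The pilot label does not remove the point, because the trial is randomised and claims a stated power at a stated level.

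**Conclusion.** The point holds in a limited form. What is certain is that 90% was derived for percentage volume change, while the stated between-group test is of volume with baseline volume as covariate and has no decisive time point. What is conditional is the size of the harm. It requires proportional effect and scatter, a true difference near 10 points, and widely varying baseline volumes; under those assumptions power falls to the figures tabulated above. Inflated type I error is a risk that the wording leaves open, not one that the plan commits to. The sample size calculation itself is not in error. The more practical weakness is the undefined decisive contrast, because it remains even if the effect is large.

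**What to change.** - Define one myoma volume per woman, for example the sum over her fibroids.
- Model its logarithm by repeated measures with log baseline volume, visit, treatment and treatment-by-visit.
- Name the treatment contrast at the end-of-treatment scan as the single primary one-sided 5% test.
- Report exp(coefficient) − 1 as the percentage difference between groups. With no change in controls, a 10-point difference is a ratio of 0.90. With controls at +5% and treated at −5% it is 0.95/1.05 = 0.905, so the two measures stay close.
- Treat other visits, single-fibroid volumes and uterine volume as supportive.

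Testing percentage change itself at the same named visit would also match the sizing, with 90.2% power by t test.

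The cost is a change of wording and a per-woman volume definition, both settled before unblinding. No new data are needed and N stays at 40.

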# Bleeding pattern, BIA and laboratory analysis will be compared using the students-t-test.

For evaluation of immunohistochemistry and molecular biology assays of uterine and breast tissue the paired and unpaired Wilcoxon´s tests will be used as appropriate.

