**3.6. Main problems anticipated**

The principal investigator has vast experience in ultrasound examination technique and the centre has also a well equipped laboratory for the experimental work concerning the myometrial tissue. Some of these analyses will be perfomed in collaboration with associate professor [name], Dept. of Obstetrics and Gynecology, UAS, Uppsala. The fine-needle aspiration for cytology will be performed and analyzed in a near-by laboratory by skilled physicians. Analyses will be performed in collaboration with [name]

Since 50 mg Mifepristone tablets are not available in Sweden, 200 mg tablets will be divided into 4 pieces containing approximately 50 mg each. An possible uneven active drug content in the 4 pieces will have no practical implication since doses ranging from 12.5 mg of mifepristone has previously been shown to be effective. Doses much higher than 25 mg have been shown not to be harmful. The long half life of mifepristone is probably also of importance to make a every-second-day approach possible. This approach has previously been successfully used in a clinical study.

Mifegyne placebo tablets are not available from Exelgyn. B-vitamin tablets will therefore be used instead of placebo. The B-vitamin tablets will not influence the studied parameters.

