### Adverse Events

Any unexpected adverse event that occur during the study will be reported to Läkemedelsverket according to LVFS 1996:17. This will also be recorded in the patient file.

The file will be kept for 15 years after end of study.

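### The t-test of means named for laboratory values is unlikely to reveal one or two women with a marked liver or haemoglobin abnormality, and is unreliable for three

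*Protocol*

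**What the plan says.** Section 3.3.1 (General outline) of the protocol states: "Blood will be drawn for analyses of liver function and hemoglobin values". The same sentence goes on to name the hormones and gives a monthly frequency for the whole draw.

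The only evaluation stated for these values is the sentence that closes the statistical text: "Bleeding pattern, BIA and laboratory analysis will be compared using the students-t-test". It does not separate liver function or haemoglobin from the hormones, and it gives no sidedness, time point or threshold. Tissue assays are sent to Wilcoxon tests instead.

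Three other places bear on the point:
- In section 3.3.1 a safety purpose is attached to the endometrial biopsies, which are "obtained prior to study start and at surgery for safety reasons and will undergo histological analyses". It is not attached to the blood tests.
- The Adverse Events section says "Any unexpected adverse event that occur during the study will be reported to Läkemedelsverket", and that such events are also recorded in the patient's file. It names neither laboratory abnormalities nor a summary by arm.
- Section 4.1 mentions a monitor outside the study who reviews the data, again without mention of laboratory values.

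**The concern.** None of the six objectives in section 3.1.2 concerns liver function, so checking for harm is the natural reason to measure it every month. Harm of that kind may show as a few women with clearly abnormal values while the rest stay as they were. That is a question about individuals, and a comparison of arm means answers it poorly: an extreme value raises the mean difference and the standard deviation together, so the test statistic stops growing.

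Haemoglobin is less clear-cut. It may serve the blood-loss objective, for which a comparison of means is reasonable, but a severe fall in one or two women would be lost in the mean in the same way.

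At stake is how a null result is read. Section 3.6 already says "Doses much higher than 25 mg have been shown not to be harmful", and section 4 calls daily treatment at higher doses safe on the basis of previous studies. A non-significant t-test on liver values could easily be taken as agreeing with those statements, when it would carry little information either way.

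**Working it through.** **Number per arm.** The protocol's inputs are "Assuming a standard deviation of 10% in the percentage volume change, 18" per group, a 10-point difference, and "with 90% power, using a one-sided 5% level test".

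n = 2(1.645 + 1.282)² × (10/10)² = 17.1, rounded up to 18; 18/0.9 = 20 recruited per arm.

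The stated figures reproduce. They were derived for fibroid volume, and serve here only to fix n.

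**Limit of the t statistic.** Let k of n women in one arm have a value M far from everyone else's, with none in the other arm, and let f = k/n. As M grows:
- mean difference → M f
- variance in the affected arm → M² f(1 − f) n/(n − 1); the other arm's variance becomes negligible
- pooled variance → half of that; squared standard error = pooled variance × 2/n → M² f(1 − f)/(n − 1)

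M cancels, so t → f / √[f(1 − f)/(n − 1)] = √[k(n − 1)/(n − k)].

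With n = 20 and 38 degrees of freedom:

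| k | t | two-sided p | one-sided p |
|---|---|---|---|
| 1 | √(19/19) = 1.00 | 0.32 | 0.16 |
| 2 | √(38/18) = 1.45 | 0.15 | 0.077 |
| 3 | √(57/17) = 1.83 | 0.075 | 0.037 |
| 4 | √(76/16) = 2.18 | 0.036 | 0.018 |

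No distribution is assumed. With 18 per arm the two-sided values are 0.32, 0.15, 0.074 and 0.034.

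**Finite values, liver enzyme.** Assumptions not in the documents: lognormal, median 0.5 × the upper limit of normal (ULN), log-SD 0.35, 20 per arm, k treated women set at 3, 5 or 10 × ULN, 10,000 to 20,000 simulated trials per setting. Percentage of trials with p < 0.05 at 3 / 5 / 10 × ULN:

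| k | raw, two-sided | log, two-sided | raw, one-sided | log, one-sided |
|---|---|---|---|---|
| 1 | 0.7 / 0 / 0 | 5 / 4 / 2 | 4 / 0.4 / 0 | 10 / 9 / 7 |
| 2 | 3 / 0.2 / 0 | 9 / 9 / 7 | 19 / 10 / 0.7 | 20 / 21 / 21 |
| 3 | 19 / 10 / 0.8 | 19 / 22 / 22 | 60 / 77 / 96 | 37 / 43 / 49 |

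On the raw scale, a two-sided test becomes less likely to be significant as the values become more extreme.

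**Finite values, haemoglobin.** Haemoglobin cannot fall without bound, so simulation is the relevant check here. Assumptions: mean 125 and SD 12 g/L, k women at 70 or 80 g/L. Two-sided: about 5%, 9% and 18–19% of trials significant for k = 1, 2, 3. One-sided: about 10%, 17–19% and 31–35%. For one woman, the two-sided rate is no better than the test's own 5% false-positive rate.

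**Would testing counts help?** Fisher's exact test, two-sided, against 0 of 20: p = 1.00 for 1, 0.49 for 2, and 0.23 for 3 (2 × 1140/9880). Five against none is the first below 0.05 (p = 0.047). Exact 95% intervals for 1, 2 and 3 of 20 are 0.1–24.9%, 1.2–31.7% and 3.2–37.9%. A count and a listing make these women visible; another significance test does not.

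**The case against.** **The sentence may not cover these tests.** The Laboratory analysis text in sections 3.3.8-10 mentions hormones and tissue but neither liver function nor haemoglobin, so the t-test could be meant for hormones alone. That reading is possible but less natural, because section 3.3.1 lists all the blood tests as one monthly draw. On the narrow reading the protocol would simply be silent.

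**Listings and shift tables belong in an SAP.** True, and their absence alone is no fault. The point is that the protocol names a method for laboratory values and makes no exception for liver function. It does not say that this is the only analysis, so adding a description contradicts nothing.

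**The t-test can sometimes pick up three women.** This stands. A reader might infer that it cannot. Two-sided, it does so in about 19% of simulated trials at 3 × ULN; one-sided on the raw scale, in 60–96%. The only sidedness in the protocol is one-sided, for the volume sample size, and nothing extends it to laboratory values.

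**Nothing calls the blood tests safety tests.** Correct. The safety purpose is an inference, strong for liver function and weaker for haemoglobin.

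**Individual cases have other routes.** Adverse event reporting, the diary card and the outside monitor mean that a serious case need not go unseen. None of them is tied to laboratory values or to a summary by arm, so they do not repair the comparison.

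**Conclusion.** The point holds in limited form. On the natural reading, the stated method for liver function and haemoglobin is a comparison of means, which is badly matched to finding a few affected women. With about 20 per arm and all affected women in one arm, the limiting two-sided p is 0.32 for one woman and 0.15 for two, and this rests on no assumed distribution. Three women are detected unreliably: limiting two-sided p 0.075, at most about 22% of simulated trials significant two-sided on either scale, and clearly better only if the test is one-sided on untransformed liver values. The simulated percentages depend on the assumed distributions; the limits do not.

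A reader might go further and conclude that the trial would declare the treatment safe on a null t-test. The protocol does not support that. It announces no such conclusion, has no safety objective, and rests its safety statements on previous studies. The risk is that a null result invites that reading, and one sentence can prevent it.

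**What to change.** Keep Student's t-test for the hormones and, if wanted, for mean haemoglobin as a measure of blood loss, and state its sidedness. Add for liver function and haemoglobin:

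- Each woman's worst on-treatment value is classified against the laboratory's reference range and tabulated by arm against her pre-treatment value.
- For haemoglobin, the change from baseline is shown as well. Section 2.1 notes that fibroids can lead to anaemia, and a below-range category alone would miss a further fall in a woman already anaemic at entry.
- Every out-of-range case is listed by arm.
- Proportions are given with exact 95% intervals as description only, without a significance test.
- A non-significant t-test on these values is not evidence of safety.

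The protocol should also say that the first monthly blood sample is taken before treatment starts; section 3.3.1 implies a monthly series but does not say so outright.

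The cost is one table and one listing from blood tests already planned, with no added subjects. The intervals will be wide, such as 3.2–37.9% for 3 of 20 and up to 16.8% even for 0 of 20, which shows how little a trial of this size can exclude.

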**3.1.2. Objectives**

The objectives of the present study are

1. To develop a new non-surgical method for treatment of uterine fibroids
2. To study the effect of mifepristone on the size of uterine fibroids
3. To evaluate factors regulating fibroid growth by comparison with untreated fibroids and normal myometrium
4. To study the effect of mifepristone on the amount of blood loss and pelvic pain in patients with fibroids
5. To study the effect of mifepristone on proliferation of breast tissue
6. To study the effect of mifepristone on body composition and cortisol levels

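### Body composition and laboratory outcomes are assigned a Student's t-test that does not say how the pre-treatment value is used; ANCOVA would be at least as efficient, to within rounding, on data already planned

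*Protocol*

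**What the plan says.** The Protocol's Statistics section gives one sentence for these outcomes: "Bleeding pattern, BIA and laboratory analysis will be compared using the students-t-test". It does not say whether the test is paired or unpaired, whether it uses final values or changes, or how several monthly values per woman are reduced to one.

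The data come from section 3.3.1:

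- Body composition and cortisol: "A 24 hour urine collection for cortisol levels will be performed and a measurement of body composition with bioelectrical impedance analysis (BIA"), followed by "These tests will be repeated after the treatment period". Each woman therefore has one value before and one after treatment.
- Blood: liver function, haemoglobin and hormones, the hormone list ending "progesterone, LH, FSH, SHBG, androstendione and DHEAS once a month". A pre-treatment draw is implied by this schedule but not stated.

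Objective 6 in section 3.1.2 rests on the first group: "To study the effect of mifepristone on body composition and cortisol levels".

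For fibroid volume, the same Statistics section specifies a repeated "measures model with the baseline volume as a covariate will be used to" compare the groups over time.

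**The concern.** The Protocol names a test for these outcomes and leaves the baseline out of it, although it uses the baseline for volume. Body cell mass, fat-free mass and total body water are fairly stable characteristics of a woman over three months. If the t-test is run on final values, much of the difference between women that the pre-treatment value could explain stays in the error term. With 18 per group, the standard error of a chance difference in baseline means is √(2/18) = 0.33 SD, which is large beside a modest treatment effect.

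The open wording is a second problem. Final-value and change-score t-tests behave very differently as the correlation varies, and the choice between them could be made after the data are seen. What is at stake is the precision of the answer to objective 6 and of the hormone, haemoglobin and liver comparisons.

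**Working it through.** **The Protocol's own figure.** The only sample size concerns volume: "Assuming a standard deviation of 10% in the percentage volume change, 18" "subjects per group will be required to detect a difference of at least 10" percentage points, with 90% power at one-sided 5%. The normal approximation gives n = 2 × (1.645 + 1.282)² × (10/10)² ≈ 17.1, so 18 per group. Allowing for 10% drop-out, 18/0.9 = 20. The non-central t power at 18 per group is 90.2%. The figure reproduces. It does not address BIA or laboratory outcomes, for which no power is claimed; it supplies only the n used below.

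**Inputs**

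- n = 18 per group (Protocol, Statistics).
- Pre-post correlation r: not in the Protocol; assumed over 0.3 to 0.9.
- Equal SD before and after, and a linear relation between the two values: assumed.
- True difference of 0.5 SD, two-sided 5%: assumed, for illustration.

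**Variance of the treatment contrast, with a t-test on final values set to 1**

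- Change-score t-test: 2(1 − r)
- ANCOVA: 1 − r²
- ANCOVA relative to change score: (1 − r²)/[2(1 − r)] = (1 + r)/2

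| r | Change vs final | ANCOVA vs final | ANCOVA vs change |
|---|---|---|---|
| 0.3 | 1.40 | 0.91 | 0.65 |
| 0.5 | 1.00 | 0.75 | 0.75 |
| 0.7 | 0.60 | 0.51 | 0.85 |
| 0.9 | 0.20 | 0.19 | 0.95 |

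ANCOVA removes more than half of the final-value variance only if r² > 0.5, that is r > 0.707.

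**Power, by non-central t**

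- Final values: non-centrality 0.5 × √(18/2) = 1.50 on 34 df, giving 31%.
- Change scores: non-centrality 1.50/√[2(1 − r)] on 34 df.
- ANCOVA: non-centrality 1.50/√[(1 − r²)(1 + 1/32)] on 33 df. The factor 1 + 1/(2n − 4) = 1 + 1/32 charges for estimating the slope.

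| r | Final values | Change scores | ANCOVA |
|---|---|---|---|
| 0.3 | 31% | 23% | 32% |
| 0.5 | 31% | 31% | 38% |
| 0.7 | 31% | 47% | 52% |
| 0.9 | 31% | 90% | 91% |

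At r = 0.95, change scores and ANCOVA both exceed 99%.

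A change-score test does well at high r but is worse than final values below r = 0.5. A final-value test wastes the baseline at high r. Over the range shown, ANCOVA matches or beats both.

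**The case against.** The strongest reply is that the Protocol never says the t-test ignores the baseline. A t-test on change from baseline fits the sentence just as well, and the volume analysis expresses results as change from baseline. On that reading the loss nearly vanishes where r is high: 90% against 91% power at r = 0.9. This stands. It rules out presenting 31% against 91% as the cost of the plan as written.

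A reader might infer that the plan discards most of the achievable precision for all these outcomes. That needs both a final-value test and r above about 0.71. The Protocol states neither. Such an r is plausible for BIA but not assured for LH, FSH, estradiol or progesterone, which vary over the cycle. A reader might also infer that the comparisons are nearly uninformative or biased. Under randomisation even the final-value t-test is valid, and the Protocol gives no between-woman SD for body composition against which a treatment effect could be judged.

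It can also be said that these are secondary outcomes of a pilot study, and that the exact form of the test could be left to an analysis plan. This limits the weight of the point. It does not remove it: the Protocol does fix a test, and the named test has no covariate. It distinguishes paired from unpaired for the Wilcoxon tests but not here. At r = 0.5 or 0.7, both forms of t-test give up power that ANCOVA would keep.

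**Conclusion.** The point holds as a matter of efficiency and of incomplete specification, not of validity. The Protocol assigns BIA and laboratory outcomes a t-test without saying how the pre-treatment value enters, although that value is collected for BIA and urinary cortisol and implied for the blood tests.

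The size depends on r and on which t-test is meant. For r from 0.5 to 0.9, ANCOVA removes 25% to 81% of the variance of a final-value test, or 25% down to 5% of that of a change-score test. The clearest benefit over final values is expected for BIA; for cycle-dependent hormones it may be small. All of this rests on assumed correlations, equal SDs before and after, and a linear relation. The change is worth making because it is nearly free, and because one method then suits both stable and variable outcomes.

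**What to change.** In the Statistics section, replace the t-test for BIA and urinary cortisol by ANCOVA of the post-treatment value on treatment group and the woman's own pre-treatment value. For the monthly blood tests, use the repeated-measures model already planned for volume, with the pre-treatment value as covariate where one is drawn, and state in section 3.3.1 whether a pre-treatment sample is taken. Log transformation of skewed analytes is optional.

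The cost is a change of wording and one degree of freedom per model. If r is zero, ANCOVA is very slightly less precise than the final-value test (variance factor 1 + 1/32, about 3%). BIA and cortisol need no new measurements; nor do the blood tests if the implied pre-treatment sample is in fact drawn.
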